## Study Endpoint

The primary endpoint of the study is time to local progression of each treated and evaluable brain metastasis. Secondary endpoints will include radiation necrosis, complete response, elsewhere-brain failure, and clinical deterioration.

## Definition of Clinical Outcomes

Local tumor recurrence versus radiation necrosis can be a difficult diagnostic dilemma. The gold standard for this diagnosis will be based upon pathological diagnosis, when available. We would recommend any suspicious lesion be investigated and biopsied. If biopsy is not possible, the patient will be followed clinically and radiographically. Cases where clinical and radiographic findings demonstrate progressive disease, as defined by the MacDonald criteria (20), will be considered as recurrent tumor. Radiation necrosis will be defined by pathology, when available. When no pathology is available, we will use the final clinical diagnosis based on clinical course and management. Complete response is defined as no residue enhancing lesion on MRI. Elsewhere brain failure is defined as appearance of brain metastases outside of prior GK region, which can be diagnosed radiographically and does not require pathological confirmation. Clinical deterioration will be assessed based on the KPS scale (Appendix A).

## Statistical Tests

As it is not certain whether the absolute values of DSC-PMR parameters after treatment or the relative change of those parameters from the baseline scan would provide the best predictive value, we will analyze our DSC-PMR data using both methods. Time to local recurrence will be modeled using the Cox proportional hazard models. The Kaplan-Meier product-limit method will be used to estimate local control probabilities. Logistic repeated measures analysis of variance will be used to model the results of MR perfusion scans from baseline to Week 1 with respect to local progression. Receiver operating characteristic (ROC) curve and area under the ROC curve will be used to estimate the predictive accuracy of different DSC-PMR parameters in predicting local recurrence after GK.

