# OBJECTIVES

## Primary Aim

To evaluate and compare changes of tumor perfusion on DSC-PMR occurring between at Week 1 after GK versus at baseline (before GK) as a predictor for time to local tumor progression. Specific quantitative values of relative cerebral blood volume (rCBV), relative cerebral blood flow (rCBF), relative peak height (rPH), and percentage of signal-intensity recovery (PSR) will be determined from each DSC-PMR. The changes of these parameters will be correlated with local control after GK to identify their predictive accuracy.

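### Section 10.4 names a logistic repeated-measures ANOVA that does not fit quantitative perfusion values and, if meant for progression yes/no, ignores follow-up time that the planned Cox model keeps

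*Protocol*

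**What the plan says.** The Primary Aim (Section 2.1) is to assess the change in perfusion between baseline and Week 1 "as a predictor for time to local tumor progression". It describes the measurements as "Specific quantitative values of relative cerebral blood volume (rCBV), relative cerebral blood flow (rCBF), relative peak height (rPH), and percentage of signal-intensity recovery (PSR"). Section 10.2 makes the endpoint a time, lesion by lesion: "The primary endpoint of the study is time to local progression of each treated and evaluable brain metastasis".

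Section 10.4 then lists four methods:

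- A Cox model: "Time to local recurrence will be modeled using the Cox proportional hazard models".
- Kaplan-Meier: "The Kaplan-Meier product-limit method will be used to estimate local control probabilities".
- The method at issue: "Logistic repeated measures analysis of variance will be used to model the results of MR perfusion scans from baseline to Week 1". The sentence ends by relating these results to local progression.
- ROC curves, where the "area under the ROC curve will be used to estimate the predictive accuracy of different DSC-PMR parameters in predicting local recurrence after GK".

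The section opens by leaving open whether "the absolute values of DSC-PMR parameters after treatment or the relative change of those parameters from the baseline scan" will predict better, and plans to analyse both. Section 10.1 gives 20 patients and about 3 lesions each, with lesions analysed as independent.

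**The concern.** A logistic model needs a categorical response. As the sentence is built, the response is the scan result, which is quantitative. The alternative is to take progression as the response, but then the repeated quantity (perfusion at two scans) moves to the covariate side and the time element of the endpoint disappears.

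The sentence bears on the primary question, whether the baseline-to-Week 1 change relates to local progression, and it stands beside a Cox model on the same question with no stated priority. There are four measures, each to be analysed as an absolute value and as a relative change, which is 4 × 2 = 8 candidate predictors. An extra model whose response is not identified adds analyst choice in a study of 20 patients. This is not a detail left for a statistical analysis plan: the protocol names a specific method, and a later plan would have to inherit the misfit or depart from the protocol.

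**Working it through.** **1. Perfusion as the response.** Section 2.1 calls rCBV, rCBF, rPH and PSR quantitative. Section 10.4 uses their absolute values and relative changes. No threshold appears in Section 5.4, Section 10 or Appendix C. The response is therefore continuous and a logistic model does not apply. A linear model would. With only two scans, its time-by-progression term is (Week 1 mean − baseline mean in progressing lesions) − (the same difference in the others), that is, a comparison of mean change between groups. That describes the groups; it does not predict time to progression.

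**2. Progression yes/no as the response.** The baseline and Week 1 scans are then covariates. With one final status per lesion, nothing is repeated within a lesion; what remains is the correlation of lesions within a patient. A lesion progressing at 3 months counts the same as one progressing at 12, and a lesion followed for 3 months without progression has no defined status. The Cox model uses both kinds of information.

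**3. The plan's own figure.** 20 patients × 3 lesions = 60, as Section 10.1 states. The point does not alter it.

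**4. How many lesions could lack a 12-month status (illustration).** The one-year local recurrence p of 27% to 33% comes from the Background section. Twelve-month mortality q is not in the documents; 30%, 50% and 70% are assumed, with constant hazards and death independent of progression.

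λp = −ln(1 − p); λd = −ln(1 − q); T = λp + λd; 1 − exp(−T) = 1 − (1 − p)(1 − q).

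Progressions seen before death = 60 × (λp/T) × (1 − exp(−T)). Deaths without progression = 60 × (λd/T) × (1 − exp(−T)).

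Example with p = 0.27 and q = 0.30: λp = 0.315, λd = 0.357, T = 0.671, and 1 − 0.73 × 0.70 = 0.489. Progressions: 60 × 0.315/0.671 × 0.489 = 13.8. Deaths without progression: 60 × 0.357/0.671 × 0.489 = 15.6.

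| Assumed 12-month mortality | Progressions seen (p = 27%; 33%) | Lesions in patients who died without progression (p = 27%; 33%) |
| --- | --- | --- |
| 0% | 16.2; 19.8 | 0; 0 |
| 30% | 13.8; 16.9 | 15.6; 15.0 |
| 50% | 11.9; 14.6 | 26.2; 25.3 |
| 70% | 9.7; 12.0 | 37.1; 36.0 |

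**5. What one possible coding would do.** Suppose those lesions were coded as non-progressing, a rule the protocol does not contain. Simulation of 400,000 independent lesions per scenario, with an assumed progression hazard ratio of 2 per standard deviation of the marker, gives a 12-month AUC of 0.710 (p = 27%) and 0.715 (p = 33%) without deaths. Under that coding:

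- Marker unrelated to death: 0.703–0.705 at 30% mortality, 0.698 at 50%, 0.692 at 70%.
- Marker also predicts death (hazard ratio 1.5 per standard deviation): 0.677–0.679, 0.655 and 0.632.

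The loss is small in the first case and becomes material only with the further assumption in the second.

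**The case against.** The strongest defence is that the sentence is loosely worded rather than wrong in substance. Its closing reference to local progression suggests that progression was the intended binary outcome, which would explain the word logistic. Local failure is recorded per lesion at 3, 6, 9 and 12 months (Section 7, Appendix B), so a clustered or discrete-time logistic model is possible, and a discrete-time one would keep follow-up time. Section 2.1 also asks that perfusion changes be correlated with local control, which a comparison by progression status would serve. This is a pilot with no stated alpha or power.

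Part of this stands. A valid logistic model could be constructed, and a group comparison is a legitimate description. But the protocol specifies no such model: it makes the scan results the object modelled and mentions no interval-by-interval outcome. The response still has to be named and the method matched to it.

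Three stronger readings are tempting, and the documents support none of them:

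- A reader might infer that early deaths are counted as non-progressing. No such rule exists. Appendix B leaves the local-failure column blank when the event has not occurred, but that is a visit form, not an analysis rule, and Section 5.5 collects overall survival, so deaths can be identified. Those lesions could equally be excluded.
- A reader might infer that follow-up time is lost for the primary endpoint. Cox and Kaplan-Meier, in the same section, retain it.
- A reader might infer two incompatible tests of the primary hypothesis. The extra model is better called redundant with the Cox model, with no stated order between them.

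**Conclusion.** The point holds as a wrongly stated analysis of limited reach. Taken literally, the logistic repeated-measures ANOVA cannot be applied to quantitative perfusion values. Taken as a model of progression yes/no with one status per lesion, it sets aside event time and censoring, leaves the handling of patients who die or leave without progression unspecified, and duplicates what Cox does better. These conclusions rest on the protocol's text and need no assumption.

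The size cannot be fixed from the documents. The 15 to 37 lesions depend on assumed mortality of 30% to 70%, and the AUC changes depend in addition on a coding rule the protocol does not contain and on assumed hazard ratios. They show why the handling should be stated, not that the trial's results would be biased by these amounts. The time-to-event analysis of the primary endpoint is not affected.

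**What to change.** Replace the sentence in Section 10.4. Relate baseline, Week 1 and change in each perfusion measure to time to local progression by the Cox model already planned, and name it as the main analysis of the primary aim. Fit baseline, Week 1 and change in separate models, since change is computed from the other two and only about 10 to 20 events can be expected in the table above. Use patient-clustered (robust) variance, because lesions in the same patient are correlated.

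If a description of perfusion over time is wanted, use a linear mixed model on the absolute values, on the log scale where they are positive and skewed, with time, progression status and their interaction, and random effects for patient and lesion. Label it descriptive and say how lesions with incomplete follow-up are classified, because that model also uses progression status. Relative changes can be negative and should not be log-transformed.

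The cost is a one-sentence amendment with no change to data collection. Clustering will widen confidence intervals slightly.

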# APPENDIX A: Karnofsky Performance Status (KPS) Scale

| **Scale** | **Description** |
| --- | --- |
| 100 | Normal no complaints; no evidence of disease. |
| 90 | Able to carry on normal activity; minor signs or symptoms of disease. |
| 80 | Normal activity with effort; some signs or symptoms of disease. |
| 70 | Cares for self; unable to carry on normal activity or to do active work. |
| 60 | Requires occasional assistance, but is able to care for most of his personal needs. |
| 50 | Requires considerable assistance and frequent medical care. |
| 40 | Disabled; requires special care and assistance. |
| 30 | Severely disabled; hospital admission is indicated although death not imminent. |
| 20 | Very sick; hospital admission necessary; active supportive treatment necessary. |
| 10 | Moribund; fatal processes progressing rapidly. |
| 0 | Dead |

# APPENDIX B: CLINICAL FOLLOW-UP FORMS

| Name of Patient: |  |
| --- | --- |
| Date of Birth: |  |
| Date of GK: |  |
| Date of Visit: |  |
| KPS Score: | (This is used to track clinical deterioration.) |
| Date of recent MRI: |  |
| Elsewhere Brain Recurrence (Outside GK) |  |
| *If yes, treatment: |  |

Local Tumor Response after Initial GK:

|  | Tumor Location | Complete Response* | Local Failure* | Radiation Necrosis* |
| --- | --- | --- | --- | --- |
| 1 |  |  |  |  |
| 2 |  |  |  |  |
| 3 |  |  |  |  |
| 4 |  |  |  |  |
| 5 |  |  |  |  |
| 6 |  |  |  |  |
| 7 |  |  |  |  |
| 8 |  |  |  |  |
| 9 |  |  |  |  |
| 10 |  |  |  |  |
| 11 |  |  |  |  |
| 12 |  |  |  |  |
| 13 |  |  |  |  |
| 14 |  |  |  |  |
| 15 |  |  |  |  |

*Please only write “X” if positive for the corresponding event, ie if tumor completely disappeared after GK, write “X” under “Complete response”. Leave the column blank if the corresponding event has not occurred.

COMMENTS:

# APPENDIX C: DSC-PMR FORMS

| Name of Patient: |  |
| --- | --- |
| Date of Birth: |  |
| Date of GK: |  |
| DSC-PMR #  (1=screening/baseline  2= date of GK  3= week 1 |  |
| Date of DSC-PMR |  |

|  | Tumor Location | rCBV* | rCBF* |
| --- | --- | --- | --- |
| 1 |  |  |  |
| 2 |  |  |  |
| 3 |  |  |  |
| 4 |  |  |  |
| 5 |  |  |  |
| 6 |  |  |  |
| 7 |  |  |  |
| 8 |  |  |  |
| 9 |  |  |  |
| 10 |  |  |  |
| 11 |  |  |  |
| 12 |  |  |  |
| 13 |  |  |  |
| 14 |  |  |  |
| 15 |  |  |  |

*rCBV = relative cerebral blood volume, rCBF = relative cerebral blood flow, rPH = relative peak height, PSR = percentage of peak-signal recovery.

COMMENTS:
